## Methods

### Study Site and Design

The PI-POC trial is a prospective observational study of children aged 0 months to 12 years presenting with symptoms of CNS infection. It also includes outpatient controls with a fever that are clinically assessed as not severely ill. The study is being conducted at the Pediatric Departments of Mbarara Regional Referral Hospital (MRRH) and Holy Innocents Children’s Hospital (HICH), Mbarara District, Uganda. MRRH is the main health facility and regional referral hospital in the southwestern region of Uganda and even receives patients from Tanzania, Rwanda, and the Democratic Republic of Congo. It is a teaching hospital for the medical faculty of the Mbarara University of Science and Technology (MUST) and has an admission capacity of 460 beds, outpatient and inpatient services, and a pediatric 70-bed ward that admits about 5000 children annually, mainly newborns and children with infectious diseases. HICH is a private pediatric nonprofit hospital established in 2009 and has a capacity of 60 beds. It offers inpatient and outpatient services, basic clinical laboratory (biosafety level 1), and counseling services. The Epicentre Laboratory is a biosafety level 3 facility, located within the campus of MUST and adjacent to MRRH. It includes parasitology, mycobacteriology, microbiology, and molecular biology (PCR, real-time qPCR, GeneXpert, BioFire FilmArray) laboratories and has biochemistry, hematology, and serology capacities. The laboratory is currently in the process of undergoing quality accreditation and operates on the principles of Good Clinical Laboratory Practice. Biobanking of samples in liquid nitrogen, –80°C and –20°C, is available on-site. Shipment of samples is conducted according to International Air Transport Association regulations.

Recruitment of patients commenced in January 2019 and was to end in June 2020. However, due to the current COVID-19 pandemic, the country underwent a total lockdown from March to June 2020, during which the study activity was paused. The study resumed mid-June and will continue until September 2020. The trial is registered at ClinicalTrials.gov (registration number NCT03900091).

### Study Participants

Children aged 0 months to 12 years who meet the case or control definition criteria, and for whom informed consent was obtained from the parent or guardian were recruited at the pediatric wards of both MRRH and HICH by the attending medical officer.

#### Case Definition

Children are suspected to have a CNS infection if they have fever or a history of fever in the past 48 hours (except for children younger than 9 months who may present with fever, normal body temperature, or hypothermia) and recent onset of any of the following at inclusion:

Nontraumatic reduced level of consciousness (in preverbal children, this corresponds to Blantyre coma score <4 for those aged <9 months, and <5 for those older than 9 months (up to 12 years of age); in verbal children, this corresponds to Glasgow Coma Scale score <15);Prostration, hypotonia/hypertonia, unexplained irritability;Severe headache (severe enough to require hospitalization);Photophobia;Neck stiffness or bulging fontanel;Prolonged, partial, or multiple seizure(s);Focal neurological signs;In children older than 18 months: Kernig sign (flexion of the hip 90° with subsequent pain in legs extension) or Brudzinski sign (involuntary flexion of the knees and hips after passive flexion of the neck);Skin petechiae; andCheyne–Stokes breathing.

Cases are recruited from the emergency department and inpatient ward of HICH and MRRH, when clinical presentation instigates suspicion of CNS infection and when the aforesaid inclusion criteria have been met. However, due to the often-ambiguous presentation of CNS infection symptoms, attending medical officers may include suspected cases even if the stated criteria are not met. The inclusion criteria of those children will be clearly mentioned in the case report form (CRF), and inclusion has to be validated by the principal investigator (EK) in Mbarara.

#### Control Definition

Controls included children aged 0 months to 12 years with a fever and not meeting the case definition, seeking care at the outpatient departments of MRRH or HICH. For every case, 1 sex- and age-matched control is included. When age matching, we allow flexibility to match up to 1 month of age for newborns, within 6 months for infants, and within a year for children from 1 to 12 years. The control definition is chosen to cater for all stated objectives of the trial, without subjecting healthy children to unnecessary and often painful diagnostic procedures.

### Biological Samples

Biosamples are collected from participants of the study, preferably before the initiation of antibiotic therapy (Table 2). In any instance, emergency care for the patients has priority over study procedures and sample collection.

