### Study Variables

A CRF for cases and controls is filled upon study enrollment. CRF includes demography, medical history, vaccination status, and use of anti-infective medicines prior to inclusion. The following information is registered by the study doctor recruiting cases: respiratory rate, consciousness according to the Glasgow Coma Scale, pulse, peripheral oxygen saturation, weight, body temperature, administered antipyretic medication (<4 hours), vomiting, neck stiffness, bulging fontanelle, unexplainable screaming, opisthotonos, central cyanosis, jaundice, inability to feed, and capillary refill time. Information regarding admission, length of stay, radiological routine clinical examination, microbiology and chemistry analyses, treatment, discharge diagnosis, and complications will be retrospectively collected from the medical records.

Laboratory data are collected by the biologist responsible for the study laboratory activities. Data entry and management are performed by the data management team in Mbarara. Deidentified data are double-entered in the REDCap (Research Electronic Data Capture) database, a web-based software for electronic capture of clinical research data [33].

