### Statistical Methods and Data Analysis

Standards for Reporting of Diagnostic Accuracy Studies (STARD) will be followed to report results [34]. For continuous variables, mean, median (IQR), SD, and maximum and minimum values will be given. Variables will be described by their percentages and CI. Clinically relevant differences in protein levels of samples versus controls will be reported using appropriate statistical methods in accordance with sample size, number, and distribution of the data. Data will be presented with 95% CI and a *P*-value of <.05 will be considered significant.

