### Limitations of the Study

Patients are recruited from 2 different hospital sites in the same area which might limit the findings to that region. Often, antibiotics are administered before LP; hence, most cases have negative results in microbiological culture. Another limitation of the study is the potential selection bias of patients during recruitment. According to the clinical picture, the medical officer may suspect a CNS infection even when not all criteria have been met. In such a scenario, cases are always validated/discussed with the principal investigator (EK) of the study in Mbarara and if included, described in detail in the CRF.

The Epicentre Research Laboratory is an advanced biosafety level 3 facility and might not be a representation of other diagnostic laboratories in Uganda. Finally, the ME multiplex PCR panel includes 14 different pathogens known to cause meningitis; however, this panel is not epidemiologically targeted to Uganda, and other agents, such as nontyphoid Salmonella, which are known to cause meningitis in children in the area [14], are not included in the panel.

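### Case plasma may be drawn after treatment more often than control plasma, and the Objective V protein comparison as stated does not separate treatment before the draw from severity

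*Protocol article*

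**What the plan says.** Biological Samples (Methods) asks for collection "preferably before the initiation of antibiotic therapy" and then states: "In any instance, emergency care for the patients has priority over study procedures and sample collection". This covers all biosamples, so a blood draw after treatment is permitted.

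The two groups enter through different doors. Case Definition: "Cases are recruited from the emergency department and inpatient ward of HICH and MRRH". Control Definition: "Controls included children aged 0 months to 12 years with a fever and not meeting the case definition", seen in the outpatient departments. Matching is one to one on sex and age, with no reference to earlier treatment.

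Objective V (Aim and Table 1) compares the proteome of severe and non-severe infection, using plasma from cases and controls. Statistical Methods and Data Analysis says: "Clinically relevant differences in protein levels of samples versus controls will be reported", by methods suited to the data, with P<.05 as significant. It does not mention treatment before sampling.

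The article refers to pretreatment in two other places. Study Variables, on a form completed for cases and controls: "CRF includes demography, medical history, vaccination status, and use of anti-infective medicines prior to inclusion". Limitations of the Study: "Often, antibiotics are administered before LP; hence, most cases have negative results in microbiological culture".

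**The concern.** Objective V looks for proteins that mark severe infection. In this design the severe group is also the group most exposed to treatment before sampling, because its members are recruited where emergency care is given and that care comes first. A protein that responds to treatment and not to severity can then differ between cases and controls and be reported as a severity marker. More children do not remove such a bias. They only make it more likely to be statistically significant.

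The authors know that antibiotics are often given early, but the Limitations section draws the consequence for culture yield only. The effect on the protein comparison is not mentioned.

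**Working it through.** The article gives no pretreatment rate, no treatment effect on any protein and no power calculation, so there is no figure to reproduce. The check has two parts.

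**1. Does the text allow unequal pretreatment at the draw?**
- Sampling order: before antibiotics is preferred, not required, and emergency care comes first (Biological Samples).
- Setting: emergency department and ward for cases, outpatient department for controls (Case Definition, Control Definition).
- Matching: age and sex only (Control Definition).
- Analysis: protein levels of samples against controls, with no stated separation by treatment (Statistical Methods and Data Analysis).
- Data: anti-infective use before inclusion is recorded in both groups, and other treatment is taken retrospectively from medical records. The time of the draw relative to treatment is not among the listed variables (Study Variables).

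Imbalance is therefore allowed. The antibiotic part can be examined with data already collected, but emergency care between inclusion and the draw may not be recoverable.

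**2. How large could the effect be? (illustration; all effect inputs are assumptions)**

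Inputs:
- share of controls treated before the draw: p0 = 20%;
- case-minus-control excess: 20, 40 or 60 percentage points, so pc = p0 + excess;
- shift in a protein among treated children: d = 0.2, 0.5 or 0.8 SD, with no true severity effect;
- n = 300 per group (Study Size section), or n = 150 per group if the abstract's 300 counts cases and controls together;
- two-sided 5% test, treating the groups as independent (matching ignored for simplicity).

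Formulas:
- false difference b = (pc − p0) × d;
- SD of the treated/untreated mixture s = √(1 + d² × [pc(1 − pc) + p0(1 − p0)]/2);
- standard error = s × √(2/n);
- chance of P<.05 = Φ(b/SE − 1.96) + Φ(−b/SE − 1.96).

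Mid-point (excess 40 points, d = 0.5 SD):
- b = 0.40 × 0.5 = 0.20 SD;
- s = √(1 + 0.25 × [0.24 + 0.16]/2) = √1.05 = 1.025;
- n = 300: SE = 1.025 × √(2/300) = 0.084, b/SE = 2.39, chance = 66.7%;
- n = 150: SE = 1.025 × √(2/150) = 0.118, b/SE = 1.69, chance = 39.4%.

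Range:

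| Excess (points) | d (SD) | False difference (SD) | Chance of P<.05, n = 300 | n = 150 |
|---|---|---|---|---|
| 20 | 0.2 | 0.04 | 7.8% | 6.4% |
| 20 | 0.5 | 0.10 | 22.3% | 13.5% |
| 40 | 0.5 | 0.20 | 66.7% | 39.4% |
| 60 | 0.5 | 0.30 | 95.0% | 72.2% |
| 60 | 0.8 | 0.48 | about 100% | 97.7% |

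With an excess of 0 points, b = 0 and this source adds no bias, whatever d is.

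**The case against.** Five points count on the other side.

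- **Controls are not well children.** They have fever, sought care and may have had anti-infectives too. What matters is the difference in rates between groups, not the rate in cases. This stands, and it is why the illustration uses an excess over a non-zero control rate.
- **The Limitations sentence concerns lumbar puncture, not the blood draw.** Blood is taken at inclusion and may come first, since lumbar puncture can be delayed. This stands: the sentence gives no rate of antibiotics before plasma sampling. The rule in Biological Samples does cover blood.
- **A reader might infer that pretreatment rises with severity, or that a treatment signal is already present in the proteome.** The documents support neither as fact. They give no pretreatment rate by severity and no protein effect. The priority rule makes the first plausible and no more.
- **The analysis model is left open.** The article allows suitable methods, including multivariate ones, and adjustment may be specified in a full protocol or analysis plan that is not shown. This stands in part: the missing model is not itself the fault. The sampling order, the unequal care settings and the matching are fixed in this text, and pretreatment is recognised as a limitation for culture only.
- **A restricted analysis has a bias of its own.** Children sampled before treatment may be milder, so a true severity marker would shrink in that subset. This stands, and it rules out requiring equal effect size in both analyses.

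**Conclusion.** The concern holds in a limited form. The plan permits case plasma to be drawn after treatment more often than control plasma, and the protein comparison as stated would not tell treatment from severity. The size cannot be derived from the documents. Under the assumptions above, the false difference runs from 0.04 to 0.48 SD. The mid-point of 0.20 SD gives about 67% false significance at 300 per group, or 39% at 150. These percentages apply to a protein that responds to treatment and not to severity, not to every protein on the array. If pretreatment rates are equal, the antibiotic part vanishes.

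This is an inexpensive improvement to an exploratory objective. It does not show that Objective V is invalid, and it is no criticism of putting emergency care first.

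**What to change.** Leave the priority of emergency care unchanged.

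1. For each case and control, code pretreatment from the existing case report form item on anti-infective use before inclusion. Where the records allow, add treatment given before the inclusion draw.
2. Report pretreatment by group.
3. Alongside the all-children Objective V plasma contrast, give (a) the contrast adjusted for pretreatment and (b) the contrast restricted in both groups to children without it. Show illness severity in the cases retained and excluded. Restriction breaks some matched pairs, so keep age and sex in the model.
4. Describe a protein whose difference does not keep its direction across these analyses as possibly treatment-related. Do not require equal size, because untreated cases may be milder.
5. Add the point to the limitations, next to culture yield.

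Cost: coding from data already collected, plus two repeat analyses. The restricted subset loses precision. Emergency care given between inclusion and the draw will be only partly controlled, because the draw time is not a listed variable and treatment is abstracted retrospectively.

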#### Cerebrospinal Fluid (Cases Only)

CSF is collected through lumbar puncture (LP) by study clinicians at MRRH or HICH. LP is delayed or not performed in the presence of contraindications (signs of elevated intracranial pressure, focal neurological signs, local infection in the area of the puncture, signs of bleeding disorders, and cardiorespiratory compromise). The collected CSF is prioritized for patient care and routine primary laboratory diagnostics at the Epicentre Research Laboratory. Residual CSF is biobanked for further analyses.

To control for possible contamination, a sample of sterile water was poured into test tubes that are used for CSF collection. This was done at regular intervals during the trial, following the same procedure as when CSF is being collected from patients.

#### Blood (Cases and Controls)

##### Cases

Up to 6 mL of venous blood is collected from cases and prioritized for routine primary diagnostics upon study inclusion. Any residue is put aside for study purposes. On day 3 of the hospital stay, an additional study sample of 1-2 mL of blood is collected and cryopreserved for the longitudinal studies.

##### Controls

Capillary or venous samples are collected for routine primary diagnostics, and additionally, up to 1 mL is sampled and cryopreserved for study purposes.

#### Nasopharyngeal Swab (Cases and Controls)

One NP swab is collected from each suspected case or control. Swabs are frozen in a medium containing skim milk, tryptone, glucose, and glycerin and will be sent to the Karolinska Institutet.

### Microbiological and Biochemical Analyses

All clinical analyses are performed on-site at the Epicentre Research Laboratory. Primary clinical analyses of CSF, such as microscopy, cytology, Gram staining (when white blood cell count is 10 cells/mm^3^ or if sample is hematic), microbiology culture, and biochemistry assay (glucose, protein, lactate) are performed. One aliquot of 200 µL of CSF is used for the multiplex ME panel (BioFire FilmArray ME Panel; BioFire Diagnostics) according to the manufacturer protocol. Blood analyses include Malaria RDT (SD Bioline Malaria Ag Pf/Pan RDT; Standard Diagnostics), HIV RDT using a sequential algorithm of Determine HIV 1/2 (Alere), followed by HIV 1/2 STAT-PAK (Chembio) for reactive samples, and SD Bioline HIV-1/2 (version 3.0; Standard Diagnostics) as a tie-breaker for discordant results, according to Uganda’s national guidelines. Other analyses included blood culture (BD BACTEC Peds Plus; Beckton Dickinson & Company), hematology (XN-550, Sysmex), biochemistry (Cobas C111; Roche), and malaria microscopy if RDT is positive. NP swabs are cryopreserved at –80°C for whole-genome sequencing and typing of relevant strains; such analyses will be conducted at the Science for Life Laboratory (SciLifeLab) and Karolinska Institutet.

**Table 2 table2:** Summary of samples and analyses in Uganda and Sweden.^a^

Specimens (type and tests)		Inclusion (Day 0)	Day 3	Clinical analyses (when/where)	Type of research analyses (when/where)
**Cases**					
	Blood: Hematology, biochemistry, HIV serology (and confirmation), malaria RDT^b^, culture, plasma biobank	6 mL	1-2 mL	Routine clinical analyses (same day at the Epicentre Laboratory).	Proteomics analyses for profiling of biomarkers including MxA^e^ (later at the SciLifeLab^f^).
	CSF^c^: Biochemistry, microscopy and cytology, culture, ME^d^-PCR panel, PCR, biobank	2 mL	—	Routine clinical analyses including ME-PCR panel (same day at the Epicentre Laboratory).	Proteomics analyses for profiling of biomarkers including MxA (later at the SciLifeLab).
	Nasopharyngeal swabs: Biobank	1 swab	—	—	Typing of bacteria and bacterial whole-genome sequencing (later at the Karolinska Institutet and SciLifeLab).
**Controls**					
	Blood: Hematology, HIV serology (and confirmation), malaria RDT, biobank	1-2 mL	—	Routine clinical analyses (same day at the Epicentre Laboratory).	Proteomics analyses for profiling of biomarkers including MxA (later at the SciLifeLab).
	Nasopharyngeal swabs: Biobank	1 swab	—	—	Typing of bacteria and bacterial whole-genome sequencing (later at the Karolinska Institutet and SciLifeLab).

^a^Additional testing for clinical care, such as TB GeneXpert or TB ZN, was performed according to clinical needs and at the discretion of the medical officer.

^b^RDT: rapid diagnostic test

^c^CSF: cerebrospinal fluid.

^d^ME: meningitis/encephalitis.

^e^MxA: Myxovirus resistance protein A

^f^SciLifeLab: Science for Life Laboratory.

### Study Variables

A CRF for cases and controls is filled upon study enrollment. CRF includes demography, medical history, vaccination status, and use of anti-infective medicines prior to inclusion. The following information is registered by the study doctor recruiting cases: respiratory rate, consciousness according to the Glasgow Coma Scale, pulse, peripheral oxygen saturation, weight, body temperature, administered antipyretic medication (<4 hours), vomiting, neck stiffness, bulging fontanelle, unexplainable screaming, opisthotonos, central cyanosis, jaundice, inability to feed, and capillary refill time. Information regarding admission, length of stay, radiological routine clinical examination, microbiology and chemistry analyses, treatment, discharge diagnosis, and complications will be retrospectively collected from the medical records.

Laboratory data are collected by the biologist responsible for the study laboratory activities. Data entry and management are performed by the data management team in Mbarara. Deidentified data are double-entered in the REDCap (Research Electronic Data Capture) database, a web-based software for electronic capture of clinical research data [33].

### Study Size, Power Calculation, and Statistical Methods

With the primary aim of this exploratory study being the evaluation of new diagnostic assays in development, a proper power calculation cannot be done. In a previous study, 459 cases with suspected CNS infection were included [14]. In half of them, a causative pathogen was identified in the CSF. Based on previous reports, we can assume that the introduction of pneumococcal conjugate immunization to the Mbarara district has halved the incidence of bacterial CNS infections caused by *S. pneumoniae* [14]. However, other causative bacterial agents of CNS infection are unlikely to have decreased in the region. We thus believe that we should be able to include approximately 160 cases in which a causative pathogen can be identified if we include the same number of cases with suspected CNS infection as in the previous study. This means that around 300 cases with suspected CNS infection will be included in this study. These numbers will be adequate for the validation of the assays.

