**Results:**

A pilot study was performed from January to April 2019. The PI-POC trial enrollment of patients begun in April 2019 and will continue until September 2020, to include up to 300 cases and controls. Preliminary results from the PI-POC study are expected by the end of 2020.

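### The projected 160 pathogen-confirmed cases depend on enrolling 459 suspected cases again; the planned 300 give about 105 to 123 on the plan's own inputs

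*Protocol article*

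**What the plan says.** The section on study size, power calculation and statistical methods builds its case in five steps.

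- Starting point: "In a previous study, 459 cases with suspected CNS infection were included".
- Yield in that study: "In half of them, a causative pathogen was identified in the CSF".
- Assumed change since then: pneumococcal vaccination "has halved the incidence of bacterial CNS infections caused by" *S. pneumoniae*, while "other causative bacterial agents of CNS infection are unlikely to have decreased in the region".
- Projection: "approximately 160 cases in which a causative pathogen can be identified if we include the same number of cases with suspected CNS infection" as in that study.
- Conclusion: "This means that around 300 cases with suspected CNS infection will be included in this study. These numbers will be adequate" for validating the assays.

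The Results paragraph of the abstract describes enrolment as "to include up to 300 cases and controls". The control definition in the Methods sets one matched control per case.

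**The concern.** The projection of 160 carries a condition: as many suspected cases as before, that is 459. The next sentence treats about 300 as the consequence of that projection, but 300 is not 459, and no input in the paragraph links the two. If 300 is the plan, 160 is not the yield to expect from it.

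The count matters because the remark that the numbers are adequate is the only justification of size in the article, and it follows directly from this count. Cases with an identified pathogen feed the sensitivity estimates for the novel assay and the commercial panel (Objectives I and II) and form the basis of the comparison of confirmed etiology (Objective III). A reader who takes 160 at face value will expect more precision than the planned enrolment gives.

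The abstract adds a second uncertainty. With 1:1 matching, its phrase can mean 300 of each group or 300 children in total.

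**Working it through.** **Inputs from the sample-size section:** 459 earlier suspected cases; 50% with a pathogen identified; pneumococcal cases halved; other bacteria unchanged; 160 projected; 300 planned. **From the control definition:** one control per case. The pneumococcal share *s* of confirmed cases is not given, so it has to be solved for.

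**1. Can 160 be reproduced from 459?**
- Confirmed before the vaccine: 459 × 0.5 = 229.5.
- Confirmed after halving the pneumococcal part: 229.5 × (1 − *s*/2).
- Setting this to 160: *s* = 2 × (1 − 160/229.5) = 0.61.

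So 160 from 459 is possible if about 61% of the earlier confirmed cases were pneumococcal. The averted cases would be 229.5 − 160 = 69.5.

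**2. Can 160 be reproduced from 300?**
- Yield required: 160/300 = 53.3%, above the earlier 50%.
- With no vaccine effect at all: 300 × 0.5 = 150.
- Suspected cases needed for 160 at the earlier yield: 160/0.5 = 320.

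None of these gives the stated pair. The nearest is 320, and it uses the yield that the paragraph has just argued no longer applies.

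**3. What do 300 suspected cases give?**

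| Assumption | Yield | Confirmed from 300 | Shortfall against 160 | Suspected cases needed for 160 |
|---|---|---|---|---|
| Suspected pool stays at 459, as the projection is worded | 160/459 = 34.9% | 104.6 | 35% | 459 |
| Averted cases also leave the pool (459 − 69.5 = 389.5) | 160/389.5 = 41.1% | 123.2 | 23% | about 390 |

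**4. Does the result depend on the solved share?** With the share set freely, 300 suspected cases give:
- *s* = 40%: 120 to 133
- *s* = 50%: 113 to 129
- *s* = 70%: 98 to 118

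All are below 160, and so is the 150 obtained at *s* = 0.

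**5. What does this do to precision?** Wilson 95% intervals for an observed sensitivity near 90%:
- 144/160: 84–94%
- 94/105: 82–94%

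**6. If 300 is the combined total** (150 cases and 150 controls):
- 150 × 160/459 = 52
- 150 × 160/389.5 = 62
- Wilson interval for 47/52: 79–96%

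**The case against.** The strongest defence is that the yield may rise. The article runs a 14-pathogen PCR panel on CSF and says that routine practice is bacterial culture only. The earlier study's methods are not shown, so 105 to 123 is a projection and not a forecast of what the laboratory will find. This stands as a caveat, but it does not repair the paragraph, which does not invoke the panel. The panel would also have to raise the implied yield by a factor of 1.30 (389.5/300) to 1.53 (459/300) to reach 160.

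A second defence is that the study is exploratory, disclaims a power calculation and states no precision target. That also stands. A reader might infer that the trial is too small, but the documents do not show this: the lower limit moves only from about 84% to 82%.

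Four other stronger readings are tempting and are not supported.

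- **A loss of two thirds of the confirmed cases.** This rests on reading the abstract as 150 cases. The Methods speak explicitly of about 300 suspected cases; the abstract is only ambiguous.
- **A further deduction for cases without CSF.** The article does say "LP is delayed or not performed in the presence of contraindications (signs of elevated intracranial pressure, focal neurological signs", with further contraindications listed. But the 50% yield was expressed per suspected case, so earlier children without CSF may already be in its denominator. The article gives no rate of missed punctures, and it says that the cultural barrier seen in the pilot was addressed by counselling.
- **A specific expected number of pneumococcal cases.** The 61% share is solved from a rounded 160 and appears nowhere in the article, so it cannot support a printed count.
- **A wrong source for the halving.** The cited study is dated 2009 to 2012 and the vaccine 2013, so the citation looks loosely placed. But the paragraph already presents the halving as an assumption drawn from earlier reports, and the cited text cannot be seen. Removing it is not justified on dates alone.

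**Conclusion.** The point holds as an arithmetic inconsistency between consecutive sentences. The figure of 160 belongs to 459 suspected cases, not to 300. On the plan's own inputs, 300 suspected cases yield about 105 confirmed cases if the suspected pool is unchanged. They yield about 123 if averted pneumococcal cases drop out of the pool, which is an added assumption. The shortfall is therefore 23% to 35%; describing it simply as one third would report only the unfavourable end. That 300 falls short of 160 does not depend on the unknown pneumococcal share. The size of the shortfall does, and it also assumes no gain in yield from the PCR panel.

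The figures of 52 to 62 apply only if the abstract's 300 is a combined total. This should be fixed, but it does not undermine the design: the effect on overall precision is small and no enrolment change is called for.

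**What to change.** In the sample-size section, replace the projection and the sentence that follows it with text along these lines:

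> About 300 children with suspected CNS infection will be enrolled. On the assumptions above, about 105 to 123 are expected to have an identified pathogen; 160 would require about 390 to 459 suspected cases. With 105 confirmed cases and a sensitivity near 90%, the 95% confidence interval would run from about 82% to 94%.

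This bases the statement of adequacy on an interval width at the expected count. If the sponsor expects the multiplex panel to raise the yield, the paragraph should say so and give the yield assumed.

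In the abstract, state whether 300 counts cases only, with as many controls again, or cases and controls together. If it is the combined total, the expected yield must be restated as about 52 to 62 from 150 cases.

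The cost is wording only. Enrolment, sampling and analysis do not change; the stated yield and precision become somewhat less favourable.
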